## Abstract

**Objectives/Aims::**

To describe the protocol of a prospective cohort study designed to answer the question: ‘Is sleep bruxism a risk factor for (peri-)implant complications?’.

**Materials and Methods::**

Our study is a single-centre, double-blind, prospective cohort study with a follow-up time of 2 years. Ninety-eight participants fulfilling inclusion criteria (planned treatment with implant-supported fixed suprastructure(s) and age 18 years or older) will be included. Sleep bruxism will be monitored at several time points as masticatory muscle activity during sleep by means of a portable single-channel electromyographic device. Our main outcomes are biological complications (i.e., related to peri-implant bleeding, probing depth, marginal bone height, quality of submucosal biofilm and loss of osseointegration) and technical complications (i.e., suprastructure, abutment, implant body or other).

**Results::**

The study is currently ongoing, and data are being gathered.

**Discussion::**

The results of this prospective cohort study will provide important information for clinicians treating bruxing patients with dental implants. Furthermore, it will contribute to the body of evidence related to the behaviour of dental implants and their complications under conditions of high mechanical loadings that result from sleep bruxism activity.

**Conclusion::**

The protocol of a prospective cohort study designed to investigate possible associations between sleep bruxism and (peri-) implant complications was presented.

## Introduction

### Implant treatment complications

Treatment with dental implants is one of the important options for patients with a partially or completely edentulous jaw. Dental implants are installed in the jawbone, and a firm, intimate, and lasting connection between implant and bone can be created (i.e., osseointegration).^
1
^ A systematic review with meta-analysis showed high 5- and 10- year survival rates of implant-supported fixed prostheses (95.2% and 86.7%, respectively, for fixed dental prostheses; 94.5% and 89.4%, respectively, for single crowns).^
2
^ However, despite these high survival rates, the same systematic review also reported a frequent occurrence of various types of implant treatment complications (up to 38.7% 5-year complication rate for fixed dental prostheses).^
2
^

Complications of the implant–suprastructure complex can be biological or technical.^
3
^ Biological complications affect the peri-implant soft tissues and bone, and are defined by pocket-probing depths, bleeding and/or suppuration on probing, and marginal bone loss over time.^
2
^ Technical complications affect the mechanical integrity of the implant and suprastructure components, and can be defined into major, such as implant fracture or loss of the prosthesis; intermediate, such as abutment fracture, abutment screw loosening or veneer fractures; or minor, such as loss of retention of the prosthesis, loss of screw hole sealing or chipping of veneering material.^
4
^

Reporting implant complications is valuable when assessing success of the implant–suprastructure complex as a whole, because, unlike single outcomes such as marginal bone loss or soft tissue parameters, it provides a more comprehensive picture of the total treatment outcome.^
5
^ Clinical and radiographical evaluations of implants and their suprastructures are generally considered to be important for the detection of early signs of these implant complications.^
6
^

### Sleep bruxism

Sleep bruxism (SB) has recently been defined as a repetitive jaw-muscle activity characterised by clenching or grinding of the teeth and/or by bracing or thrusting of the mandible during sleep.^
7
^ It is suggested that jaw-muscle contractions are a natural activity during sleep, and that SB episodes are observed in most individuals.^
8
^ Up to 37% variability in SB outcome measures has been reported in sleep bruxers,^
9
^ suggesting that SB has a time-variant nature.

Polysomnography with audio-visual recordings (PSG-AV) is necessary to achieve a definite diagnosis of SB,^
7
^ according to established cut-off criteria.^
10
^ However, this technique is costly and often impractical to perform, leading to the use of less accurate methods for diagnosing SB. In clinical practice and research settings, this involves self-report instruments, clinical examinations and electromyographic (EMG) recordings of masticatory muscle activity during sleep.^
7,11
^

Epidemiological studies based on self-reports have found that ~12.8% of the adult population reports ‘frequent’ SB.^
12
^ To date, only a single study assessed the prevalence of SB based on PSG recordings and the above-mentioned cut-off criteria in a large population sample.^
13
^ On the basis of single-night PSG recordings, the prevalence of SB in an adult population was 7.4%, regardless of self-reported bruxism complaints.^
13
^ In the future, studies implementing diagnostic methods capable of capturing the time-variant nature of SB should lead to more accurate figures about the prevalence of SB.^
9
^ Prevalence data based on sound criteria are important. However, the clinician interested in the consequences of SB should be aware that, even individuals who, after one or several PSG recordings, would not officially be characterised as sleep bruxers, can present (mild) bruxism activity during sleep.^
14
^

### SB and implant treatment complications

SB is considered an important source of loading applied to implants and their suprastructures, and it is a longstanding concept that SB can lead to biological and technical complications.^
3
^ Two recent systematic literature reviews point towards the notion that bruxism can contribute to the occurrence of mainly technical failures of implant treatments,^
15,16
^ while there is no sound evidence that bruxism is related to biological implant complications.^
15
^

However, a causal relationship between SB and (peri-)implant complications has not yet been demonstrated.^
15,16
^ This lack of sound evidence is the consequence of mainly two factors. First, up to the present time, there is no study with the specific design to assess the effect of bruxism on dental implants. Studies that have included bruxism as one of the factors contributing to complications show a large variation in terms of both the technical and the biological outcomes of implant treatments, so that their comparability is compromised.^
15,16
^ Second, there are issues regarding the internal validity of those studies, such as an inadequate distinction between sleep and awake bruxism, and insufficient diagnostic approaches of SB.^
3,15,16
^ On the basis of the assumption that SB can lead to complications, clinicians are so far instructed to be cautious, and are guided by expert opinions regarding practical aspects of implant treatments in patients with (suspected) bruxing behaviour.^
15
^ These guidelines include advices on implant and suprastructure characteristics, such as the number, length and diameter of implants, the material of the suprastructure, and the occlusion and articulation patterns.^
3
^ Expert opinions represent the lowest grade of evidence and cannot, therefore, fulfil modern clinicians’ needs for evidence-based decision-making.

The lack of high-level evidence also affects researchers, as suspected bruxism is often—but not always—an exclusion criterion in studies concerning the outcomes of dental implant treatments.^
3
^ Consequently, the populations in such studies may significantly differ from each other, which undermines the ability to compare their outcomes in an unequivocal way. Furthermore, if SB proves indeed to have detrimental consequences for the success of implant treatments, it is an important factor to be considered when designing relevant studies.

### Mechanical loading and biological parameters

Clinical studies, literature reviews and expert consensus papers^
17–19
^ report that formation and maturation of a microbial biofilm around an implant is an important aetiologic factor in the pathogenesis of the peri-implant infectious diseases ‘mucositis’ (i.e., inflammatory process in the mucosal tissue) and ‘peri-implantitis’ (i.e., inflammatory process additionally characterised by marginal bone loss). Submucosal biofilm associated with these diseases has been reported to present low species diversity, with fewer numbers of bacterial species found around diseased implants, compared to the biofilm found around healthy implants.^
20
^ Other factors related to the occurrence of peri-implant disease include smoking and a history of periodontitis.^
21
^

On the basis of current literature, it is not fully known whether and how mechanical implant loading contributes to peri-implant tissue complications (i.e., inflammation and bone loss). Several clinical studies^
22,23
^ suggest that high mechanical stress, exceeding the biological load-bearing capacity of an osseointegrated oral implant,^
24
^ is associated with loss of marginal bone or even loss of the osseointegration around the implant. More recently, a review on animal studies found differences in the histological features between plaque- and overload-induced peri-implant bone loss.^
25
^ However, as yet, causative relationships between mechanical loading and peri-implant biological complications have not been established, due to a general lack of clinical studies with an appropriate design to assess the effect of excessive loading on dental implants,^
26
^ and poor definitions of the loading conditions (e.g., poor approaches to diagnose parafunctions such as SB).^
15
^

It remains unclear if, and to what extent, loading and microbial factors interact in the process of peri-implant tissue destruction.^
24
^ Animal experimental data suggest that high loading of clinically stable dental implants is associated with marginal bone loss in the case of inadequate plaque removal, while when plaque control is sufficient, this loading might lead to an increase of bone density around the implant.^
27
^ In addition, data revealing unique and unsuspected microbial communities around failing implants have recently been presented,^
20
^ whereas sparse human clinical data suggest a possible different microbial profile between implants failing due to mechanical overload, as compared to implants failing due to peri-implant infection.^
28,29
^ However, thus far, research supporting these suggestions is not conclusive.^
30
^ Investigating the time-dependent associations between mechanical forces (such as those attributed to SB), the composition of microbial communities and host response will enhance our insight into the pathogenesis of peri-implant disease.

### Objective of the present study

To contribute to the understanding of the time-dependent associations between SB and complications of dental implant treatments, we aim to perform a prospective cohort study. Our main aim is to answer the research question: ‘Is sleep bruxism a risk factor for (peri-)implant complications?’. SB will be monitored by measuring masticatory muscle activity during sleep. The investigation will have two main outcomes, namely, technical complications and biological complications. As to avoid variation in the outcomes caused by failing retention of removable suprastructures, we will confine our study population to patients treated with fixed suprastructures.

The following null hypotheses are formulated: (1) Sleep bruxism is not associated with the occurrence of technical complications. Outcomes of interest are: suprastructure complications, abutment complications, implant fractures or other technical failures (see ‘Variables’ paragraph for a more comprehensive description of all variables), and (2) SB is not associated with the occurrence of biological complications. Main outcomes related to this hypothesis are: differences in marginal bone height, peri-implant bleeding on probing, pocket depths and loss of osseointegration.

Our secondary aim is to examine whether there is an association between SB activity and the composition of peri-implant submucosal biofilm. For this purpose, the null hypothesis is: SB is not associated with species diversity of peri-implant submucosal biofilm. The main outcome will be peri-implant submucosal microbiome diversity.

### Study design

The study has a prospective, double-blind design and will be performed in the Academic Centre for Dentistry Amsterdam (ACTA), The Netherlands. Aimed duration of the study is 3 years: 1-year sampling period and 2 years of follow-up. Participants of the study will receive one or more dental implants, which will be loaded with a fixed dental prosthesis for replacement of one or more lost teeth. Baseline assessment (T_1_) of each participant will take place after the healing period of the implant(s), at the appointment of taking the impressions for the prosthesis. Afterwards, assessments will take place within a follow-up period of 2 years at pre-fixed time intervals (2 weeks; T_2_, 6 weeks; T_3_, 3 months; T_4_, 12 months; T_5_, and 24 months after baseline; T_6_, see Table 1). These assessment intervals match those of the regular clinical procedures at ACTA, with the exception of T_3_, which represents an additional examination. Recurrent ambulatory EMG recordings for the diagnosis of SB will be performed by the participants in their home environment at T_1_, T_3_ and T_5_. Clinical measurements will be performed by one examiner (MT) at ACTA. This examiner, as well as the participants, will be blinded for the main predictor of the study, i.e., SB diagnosis based on EMG recordings.

## Materials and methods

### Ethical considerations and registration of study

All study procedures are performed according to the guidelines issued in the Declaration of Helsinki. Approval of the research protocol by the Medical Ethical Committee of the Vrije Universiteit Amsterdam was obtained (METC—VUmc ref.: 2011-245). The Dutch Healthcare Inspectorate acknowledged that the obligation for notification of the Dutch Healthcare Inspectorate prior to the start of the clinical investigation was fulfilled. The research is included in the Netherlands Trial Register (Trialregister.nl, reference no.: 4930) and is registered at the US National Institutes of Health (ClinicalTrials.gov Identifier: NCT02410681). Extensive documentation of all standard operating procedures is performed, following ISO 14155.2011 criteria. Collected data will be digitally stored using ALEA Data Management-version 4 (ALEA Data Management, FormsVision, Abcoude, The Netherlands). ALEA provides online data management tools for use in clinical trials and enables tracking of all changes made to previously inserted data.

### Participants

Participants will be enrolled in the study if they fulfil the inclusion and exclusion criteria, agree to participate, and sign the informed consent form. Participants will be recruited from the clinic of the Department of Oral Implantology and Prosthetic Dentistry of the ACTA. This department treats patients situated in the greater Amsterdam area. Inclusion criteria are: a planned treatment with implant-supported fixed suprastructure(s) and age 18 years or older. Exclusion criteria are: opposing teeth of implant-supported fixed suprastructure(s) are restored with removable artificial teeth; patients categorised in the classes 3 or higher according to the American Society of Anesthesiologists (ASA) system for classification of physical status;^
31
^ use of an occlusal splint, mandibular repositioning appliance or any other bruxism mitigating device during sleep; active periodontitis at the time of implant placement; known allergy to the EMG device electrode material; usage of a pacemaker; and swollen, infected or inflamed tissues or skin eruptions, e.g., phlebitis, varicose veins etc. in the placement area of the EMG device electrode. Pregnant women will not be treated with dental implants. Pregnancy after the placement of implants will not be a reason to stop participation of the subject in the study.

All patients of the clinic of Oral Implantology and Prosthetic Dentistry for which one or more implants are planned will be screened for fulfilment of the inclusion and exclusion criteria and willingness to participate in a clinical study. Eligible patients will be thoroughly informed about the study, upon which they will be given 1-week time to consider participation. Written informed consent will be obtained prior to enrolment of a patient in the study. Participation is voluntary and can be withdrawn at any time, without consequences for the course of treatment.

### Sample size

To analyse the association between predictors and outcome variables for both our main aim and our secondary aim, multilevel regression analyses will be used.^
32
^ Therefore, we will use the suggested formula ‘50+8*k* (*k*; number of predictors)’ for the calculation of our sample size.^
33
^ On the basis of that formula, this study (with six predictors) will need a minimum sample size of ‘50+48=98’ participants.

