#### Single/multiple analysis

Our hypotheses will be tested using multilevel regression analyses.^
32
^ As for the main aim of the study, hypotheses about associations between SB and the occurrence of technical complications or loss of osseointegration will be tested by using a Cox proportional hazards regression model.^
48
^ Possible associations between SB and bleeding on probing, pocket depths and marginal bone height will be tested by means of linear regression analysis. Likewise, for our secondary aim, possible associations between SB and microbiome diversity will be tested by means of linear regression analysis. The regression models will be expanded to examine the effects of confounders and covariates on the associations between main predictor and main outcomes. We aim to adjust our analysis for dependency of data, which arises from the fact that multiple implants can be placed in one subject, thus violating the assumption of independent observations.^49
^

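### The minimum of 98 participants rests on a rule with no event input, so it does not justify the two Cox analyses (technical complications and loss of osseointegration)

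*Protocol article*

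**What the plan says.** The Sample size section first fixes the scope of the calculation: "To analyse the association between predictors and outcome variables for both our main aim and our secondary aim, multilevel regression analyses will be used". It then names the rule, "we will use the suggested formula ‘50+8*k* (*k*; number of predictors)’ for the calculation of our sample size", and the result: "this study (with six predictors) will need a minimum sample size of ‘50+48=98’ participants". No event rate, target effect, significance level, power or number of implants per participant enters.

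The Single/multiple analysis section assigns the models. For the main aim, "associations between SB and the occurrence of technical complications or loss of osseointegration will be tested by using a Cox proportional hazards regression model". Bleeding on probing, pocket depths and marginal bone height, and microbiome diversity for the secondary aim, go to linear regression. All models are then to be expanded with confounders and covariates, with adjustment for several implants in one person.

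The Study design section gives 2 years of follow-up. The only background rates are in the Introduction, under Implant treatment complications: "up to 38.7% 5-year complication rate for fixed dental prostheses", and 5- and 10-year prosthesis survival of "95.2% and 86.7%, respectively, for fixed dental prostheses; 94.5% and 89.4%, respectively, for single crowns".

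**The concern.** The article makes a positive claim: 98 is enough for both aims. For the linear outcomes, a rule based on participants and predictors at least counts the right kind of unit. For a Cox model it does not, because participants without an event add little to the precision of a hazard ratio. The same 98 people could supply fifty events or two, and the rule would return the same answer.

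This is more than detail left to an analysis plan that is not shown. The stated justification does not fit the stated model, and the mismatch covers the whole of the first main hypothesis plus one component of the second. If few events occur and the model is filled with covariates, the hazard ratio for SB will have a very wide interval. A non-significant result would then carry little information on whether SB is a risk factor, which is the study's central question.

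**Working it through.** **Stated figure.** 50 + 8 × 6 = 98. It reproduces, so the arithmetic is not at fault.

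**Assumptions (none in the article).** Constant hazard; one first event per participant; no dropout; two-sided 5% level; 80% power. Neither Cox endpoint has its own rate. The 38.7% is an upper figure covering various types of complication in fixed dental prostheses. Prosthesis survival is only a proxy for keeping osseointegration.

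**Any complication, 2 years.** Risk = 1 − (1 − 0.387)^(2/5) = 0.178; × 98 = 17.4 participants with an event.
- Half the 5-year rate (19.35%): risk 0.082, 8.1 events.
- Dropout of 10% to 20%: 15.7 to 13.9 events.
- Two to three implants each, treated as fully independent: 34.8 to 52.3 events. This is a ceiling, since the article itself says implants in one person are dependent.

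**Events per predictor, participant level.** 17.4/6 = 2.9; 8.1/6 = 1.3. The article does not list its six predictors. Coding the variables under Covariates and confounders as SB 1, smoking 3 (four categories), awake bruxism 1, plaque 1 and periodontal 2 gives 8 degrees of freedom, and 17.4/8 = 2.2.

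**Loss of osseointegration, by the survival proxy.**
- 5-year figures: 98 × (1 − 0.952^0.4) = 1.9; 98 × (1 − 0.945^0.4) = 2.2.
- 10-year figures: 98 × (1 − 0.867^0.2) = 2.8; 98 × (1 − 0.894^0.2) = 2.2.
- Two to three independent implants each, 5-year figures: 3.8 to 6.6 events, at most about 1 per predictor.

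**Detectable hazard ratio for continuous SB, before adjustment.** HR per SD = exp((1.960 + 0.842)/√events).

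| Events | HR per SD at 80% power |
|---|---|
| 17.4 | 1.96 |
| 8.1 | 2.68 |
| 2.2 | 6.6 |
| 1.9 | 7.6 |

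If covariates explain 20% of the variance of SB, 17.4 events give exp(2.80/√(17.4 × 0.8)) = 2.12.

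**Behaviour of the adjusted models (simulation).** 98 people, independent normal covariates, true HR 2 per SD. With 17 events and six predictors, the median estimate was 2.15, the 95% range 1.15 to 4.5 and interval coverage 92%: modest bias, poor precision. With two events, the partial likelihood had no finite maximum in 32% of data sets with six predictors and 59% with eight. A repeat with another seed gave 28% and 57%, and 8% and 21% with three events.

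**What 98 gives in a linear model.** With six predictors and independent single-level observations, power is 0.80 for f² = 0.15 (R² = 0.15/1.15 = 0.13), and the smallest detectable partial r² for SB alone is 7.6%. The planned models are multilevel, so these are reference values only.

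**The case against.** The best defence is that the event counts are not the article's. The complication rate is an upper figure for a different mix of events, prosthesis survival is not osseointegration, and the technical list includes minor events such as loss of a screw seal. The true rate could lie on either side. Analysing per implant would also raise the counts. This stands, and it is why the figures above are ranges under labelled assumptions. It does not rescue 98, because the rule would give 98 whatever the rate.

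Some stronger readings are tempting, and the article does not support them:
- **That 50+8k is a linear-regression rule wrongly borrowed.** The article calls it a suggested formula in a multilevel context, and its source is not at hand. Only the missing event input can be shown.
- **That the first hypothesis cannot be tested with 98.** The Single/multiple analysis section implies a start from SB alone before expansion. It does not say that all six predictors enter every Cox model.
- **That a Cox model with two events cannot be fitted.** With one predictor it usually can, though almost uselessly. With six it often has no finite estimate.
- **That the detectable hazard ratio is 7.5 to 13.** This needs SB as a yes/no exposure at general-population prevalences of 12.8% or 7.4%. The article speaks of an SB diagnosis but derives two continuous measures, and states no cut-off for classifying participants.

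**Conclusion.** The point holds in limited form. The stated minimum is not justified for the Cox analyses, and this follows from the text alone.

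For loss of osseointegration the conclusion is firm in every scenario examined: about 2 to 3 events at participant level, and up to about 7 from the 5-year figures with three independent implants each, are too few for an adjusted Cox model.

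For technical complications it is conditional. With about 8 to 17 events, an SB-only or sparse model remains usable for large effects, while a six-predictor model would be imprecise. A reader might infer that 98 participants are useless for the first hypothesis; that goes too far. The sizes rest on constant hazard, one event per participant, no dropout, and background rates that match neither endpoint exactly. Should-fix.

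**What to change.** 1. Limit the claim for 98 participants to the outcomes analysed by linear regression.
2. For technical complications, state the expected number of events and the detectable hazard ratio as a range with its assumptions (on the rates above, about 8 to 17 participants with an event and about 2.7 to 2.0 per SD before adjustment). Enter SB as a continuous measure, and keep the Cox model sparse, for example with penalisation, allowing for clustering within participant.
3. Replace the Cox test for loss of osseointegration with its incidence and an exact interval, labelled descriptive. For illustration, 2 of 98 participants is 2.0%, 95% interval 0.2% to 7.2%. If reported per implant, the interval must allow for clustering.

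The cost is rewording of the Sample size and Single/multiple analysis sections, a less favourable stated figure for the first hypothesis, and less covariate adjustment in the technical-complication model. No participants are added.
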